#### Stroke survivors

Age (years); sex (male/female); pre-morbid walking status (independent/walks with an aid); marital status (single, married/remarried, separated, widowed, divorced); occupation pre-stroke (e.g. school teacher, retired); current work status (full-time paid, part-time paid, causal, registered sick/disabled, retired, unemployed, student); medical history (diabetes, arthritis etc.); geographical location (post code) education (year count); date of stroke; assistive device use (no device/stick/tripod/elbow crutches/zimmer frame/delta frame/four wheeled walker/wheelchair/other); Rivermead Mobility Index [27]; Fatigue Assessment Scale [28]; Warwick-Edinburgh Mental Well-being Scale (WEMWBS) [29]

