#### Mode of delivery

The self-management intervention programme will be supported by HCPs (e.g. physiotherapists, occupational therapists, rehab assistants) working in community stroke teams. The HCPs will all have specialist knowledge in community stroke rehabilitation. The first session/s will be delivered face-to-face with review sessions delivered either face-to-face or by telephone.

The intervention programme will be initiated once the stroke survivor is moving towards supported self-management and a need to move more and sit less has been highlighted. The time from stroke will vary dependent on needs of the stroke survivor/health care professional’s opinion on the best timing/availability of resources. Participants may still be receiving rehabilitation from the community stroke teams at the same time as the delivery of the intervention.

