### Safety

The safety of the intervention will be evaluated by examining the occurrence of serious adverse events. This study will only report adverse events which are considered to be serious.

The standard definitions for serious adverse events will be used in this study:

*Serious adverse event (SAE)*: an untoward occurrence that:
Results in deathIs life-threatening (refers to an event in which the subject was at risk of death at the time of the event; it does not refer to an event which hypothetically might have caused death if it were more severe)Requires hospitalisation, or prolongation of existing hospitalisationResults in persistent or significant disability or incapacityIs otherwise considered medically significant by the investigator

Medical judgement will be exercised in deciding whether an adverse event is serious in other situations. Important medical events that are not immediately life-threatening or do not result in death or hospitalisation but may jeopardise the patient or may require intervention to prevent one of the other outcomes listed in the definition above should also be considered serious.

Serious adverse events *exclude*:
Pre-planned hospitalisationsScheduled treatment for pre-existing conditions.

Capture of potential SAEs will take place at face-to-face review sessions by including the following questions in the outcome pro forma: “are there any new medical problems since the last study visit?” For any events which fulfil the criteria to be a SAE and are unreported, the study SAE form will be completed.

Events considered to be SAEs will subsequently be documented onto a separate study SAE form, and a causality and expectedness assessment will be performed. As study investigators or other members of the research team may become aware of SAEs at times other than at review assessment appointments, the SAE form will also be used to directly capture these events.

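### The one printed question for eliciting serious adverse events asks only about new problems, so serious worsening of an existing condition may go unelicited

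*Protocol article*

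**What the plan says.** All of the following is in the protocol article.

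- **Safety, definition.** An SAE is an untoward occurrence that is fatal or life-threatening, leads to or prolongs a hospital stay, causes lasting or important disability, or is judged medically significant by the investigator. Two things are carved out: admissions planned in advance, and treatment already scheduled for conditions the participant had before.
- **Safety, scope.** "This study will only report adverse events which are considered to be serious".
- **Safety, active capture.** "Capture of potential SAEs will take place at face-to-face review sessions by including the following questions in the outcome pro forma". One question follows: "are there any new medical problems since the last study visit".
- **Safety, second route.** Staff may learn of an SAE outside a review. In that case, the section says, "the SAE form will also be used to directly capture these events".
- **Data collection, Stroke survivors.** Baseline data include "medical history (diabetes, arthritis etc" and similar, so conditions already present are expected and recorded.
- **Stroke survivor intervention, Mode of delivery.** The first contact is in person, with "review sessions delivered either face-to-face or by telephone".
- **Objectives and Data analysis, Objective 2.** Safety is one component of the feasibility of delivery and will be described.

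**The concern.** The definition and the question do not cover the same events. The definition turns on what happened to the participant: an admission, a disability, a threat to life. The question turns on whether the problem is *new*. An event can be serious and unplanned without being new in the participant's eyes, for example an emergency admission for a flare of a condition listed at baseline.

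This matters in this population. Every participant has had a stroke and many will have other long-term conditions. The exclusion criteria remove contraindications to activity, with unstable heart disease as the example, so people with stable disease can enter. The intervention aims to increase activity. Serious worsening of something already present is therefore a harm the study would want to see, and it is the one that the word *new* tends to screen out.

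Safety is evaluated only through SAEs and non-serious events are not reported, so no general adverse-event record exists from which a missed event might be recovered. The study has at most 35 stroke survivors and no comparator, so the safety description will rest on very few events.

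**Working it through.** No figure in the plan bears on this point and there is none to reproduce. The check compares the definition, the exclusions, the question and the other capture route, all in the Safety section, for each kind of event.

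| Event since the last visit | SAE under the definition? | Exempted? | Would the printed question bring it out? |
|---|---|---|---|
| Unplanned admission for a new problem | Yes | No | Ordinarily yes |
| Unplanned admission for worsening of a baseline condition | Yes | No | Not reliably: *no* is a truthful answer |
| Worsening of a baseline condition, no admission, but lasting disability or medically significant | Yes | No | Not reliably, for the same reason |
| Worsening of a baseline condition, no seriousness criterion met | No | – | Not relevant to the safety outcome |
| Injury, for example from a fall, that meets a seriousness criterion | Yes | No | Ordinarily yes, as a new problem; not named explicitly |
| Injury that meets no seriousness criterion | No | – | Not relevant to the safety outcome |
| Admission planned in advance, or treatment already scheduled | No | Yes | Not relevant |

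The mismatch is confined to the second and third rows. In both, the definition counts the event, neither exemption removes it, and the question as worded does not ask about it.

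**Does the second route close the gap?** It lets staff complete the SAE form whenever they learn of an event, so reporting does not depend on a positive answer. It does not ask anyone anything, however. It works only if staff come to know. The Mode of delivery section says participants may still be in rehabilitation with the community team during the intervention, which makes this likely for some and leaves it uncertain for others.

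**Where is the question asked?** The Safety section ties it to in-person reviews, while Mode of delivery allows review by telephone. The abstract describes at least two face-to-face sessions, including a review, so the two descriptions should be reconciled. A telephone review followed by an in-person one loses little, because the question looks back to the last visit. A participant whose last review is by telephone would not, on the stated text, be asked about the final interval.

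**Direction.** Unelicited events can only lower the SAE count. Nothing in the wording would raise it.

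**The case against.** The strongest reply has four parts.

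1. *Other prompts may exist.* The text announces questions in the plural and prints one. The pro forma is not shown and the article is condensed. This stands as a limit: the point concerns the only question printed, and it cannot be said that no other is asked. It does not excuse the wording of the question that the article does fix.

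2. *Treating staff will know.* The intervention is delivered by the community stroke teams; mobility, fatigue and well-being are reassessed at reviews; intercurrent illness may lead to a pause or withdrawal, and reasons for withdrawal are sought. These routes make it less likely that a serious event passes unseen. None of them asks about admissions or worsening, so they reduce the gap without closing it.

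3. *Most events are covered anyway.* A reader might infer that the question misses injuries and unplanned admissions generally, and that worsening or injury always counts as an SAE. The documents support neither. A participant hurt in a fall, or admitted with something new, would ordinarily mention it. Worsening or injury is an SAE only when a seriousness criterion is met. The gap is limited to serious worsening of, or unplanned admission for, a condition already present.

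4. *Little turns on it.* Safety is only described, and none of the progression criteria uses an SAE count. This is correct and keeps the point modest. The description will still inform the design of the larger evaluation, so it should be as complete as one line of a form can make it.

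**Conclusion.** The point holds in its narrow form. The printed question is narrower than the protocol's own SAE definition, and the difference falls on serious events arising from conditions present at baseline. For these, capture rests on a passive route, and the SAE description under Objective 2 may be biased downwards.

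The size of the bias cannot be derived from the documents, which give no admission rate, no split between new and known causes, and no likelihood that staff would hear of an event. A reader might infer that the gap could turn a study with some SAEs into one with none. An illustration does not bear that out. Assume that 10% of 35 participants have an unplanned admission, and that 30% to 70% of these are for a known condition or an injury and are all missed:

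- admissions: 0.10 × 35 = 3.5
- missed: 0.30 × 3.5 = 1.05 to 0.70 × 3.5 = 2.45
- still captured: 3.5 − 2.45 = 1.05 to 3.5 − 1.05 = 2.45

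Both percentages are assumptions. Counting every such event as missed is pessimistic, since it gives no credit to the question for injuries or to staff awareness. Even so, the expected captured count stays above zero. The conclusion rests on the wording alone, and on the assumption that the printed question is the one used.

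**What to change.** Reword the question on the outcome pro forma so that it matches the definition, for example: *Since the last study contact, have you had any new medical problem, any worsening of an existing problem (including any injury), or any unplanned hospital admission?* Ask it at every review, including those by telephone, and amend the Safety section to say so. A positive answer leads to the existing seriousness check and SAE form. The definition, the exemptions and the reporting timelines stay as they are. If the full pro forma already carries such prompts, printing them in the Safety section is enough.

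The cost is one reworded line, a few seconds at each review, possibly a minor amendment, and some additional answers to triage that will prove not to be serious. Those answers need not be reported, since the restriction to serious events is unchanged.

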### Data analysis

#### Objective 1

Stroke survivor recruitment rate/month (total per site) and attrition rates/site and reasons will be described. HCP recruitment will be described as number of HCPs recruited compared to number of eligible HCPs in each team. Non-completion of training programme (e.g. face-to-face training, workbook, feedback) will be described as a percentage of non-completers out of the total of HCPs recruited.

#### Objective 2

The profession of the HCP delivering the intervention; the number and time taken (minutes) for face-to-face/telephone intervention delivery, the application of the different intervention components applied (e.g. self-monitoring tools, activity selection) and safety reporting will be described.

#### Objective 3

Completeness of outcome measure data collection including questionnaires will be described (number and percentage). Summary descriptive statistics (e.g. mean and standard deviation, median and interquartile range, 95% confidence interval as appropriate) will be used to describe stroke survivor baseline demographics and psychological well-being (Warwick-Edinburgh Mental Well-Being Scale), fatigue (Fatigue Assessment Scale) and mobility (Rivermead Mobility Assessment) at baseline and review.

#### Objective 4

Closed questionnaire data from stroke survivors will be coded and summarised. Open-ended questions have also been included in order to encourage full, meaningful answers using the participants own words that might potentially offer insights or issues not captured in the closed questions, yielding more accurate information to inform future studies. Answers to open questions will be thematically explored in order to identify, analyse and report patterns (themes) within the data.

Thematic analysis has been chosen to analyse the interview data as it is a flexible method that allows themes to emerge from the data [33] and has previously been used to analyse data following exercise interventions [34] and physical rehabilitation following stroke [35]. This rigorous thematic approach can produce an insightful analysis that answers particular research questions [33]. Thematic analysis is one of the most commonly used methods of analysing qualitative data, as it is simple, is less time consuming and has a flexible approach. NVivo software will be used to aid analysis. The data will be transcribed and then repeatedly read and coded by two researchers independently within a framework of a priori issues and those identified by stroke survivors or emerging from the data. Any divergence between coders will be discussed on an on-going basis to inform the analysis and resolve differences in the interpretation of data. Analysis will be discussed at regular meetings of the research team to identify areas for closer consideration (including negative case analysis) and to enhance credibility of the thematic framework and interpretation [32, 36].

#### Objective 5

Delivery, receipt, enactment and adherence to the intervention by stroke survivors and HCP will be analysed from completion of face-to-face baseline and review sessions, case report forms, goal summary sheets and audio recordings of the face-to-face delivery of the intervention. This data will be used to determine the fidelity of the delivery, receipt, enactment and adherence to the intervention.

#### Objective 6

Closed HCP questionnaire data from pre and post the training programme will be coded and summarised. Open-ended questions have also been included in order to encourage full, meaningful answers using the participants own words that might potentially offer insights or issues not captured in the closed questions, yielding more accurate information to inform future studies. Answers to open questions will be thematically explored in order to identify, analyse and report patterns (themes) within the data.

#### Objective 7

Audio recordings of HCP and stroke survivor baseline or review sessions will be transcribed verbatim and used alongside HCP recorded written notes on aspects of intervention delivery. One of the research team trained in the use of the Behaviour Change Taxonomy Version 1 (BCT v1) [21] and an expert coder will independently code all consultation transcripts and written notes to assess skill acquisition (for feedback purposes) and fidelity of delivery of each specific behaviour change technique. A coding frame/fidelity checklist based on the BCT v1 will be used to identify whether each BCT was delivered as planned. Where discrepancies in coding exist, the researcher and expert coder will meet to resolve these via discussion. The percentage of positive agreement will be calculated to assess inter-rater reliability.

## Discussion

The main aim of this feasibility study is to determine the feasibility, acceptability and fidelity of a multifaceted behaviour change intervention targeting free-living physical activity and sedentary behaviour in community dwelling adult stroke survivors. The most effective methods for improving long-term physical activity and reducing sedentary behaviour after stroke have yet to be ascertained. Theory-informed interventions are shown to improve physical activity in other long-term conditions and may be effective post-stroke. The intervention tested within this study has been developed with the use of theory and behavioural mapping, increasing potential for efficacy. The content of stroke rehabilitation interventions is often poorly described [37]. Content of this current intervention has been described using the TIDieR framework [20] which will enable further testing of the components of the intervention and translation of future results. Previous stroke rehabilitation research has been limited by a lack of measurement of fidelity, e.g. whether interventions are delivered as intended. In this study, there is a focus on ensuring and measuring fidelity, which will enable understanding of whether of intervention delivery and inform future knowledge in this field and the iterative development of the intervention to enable future testing.

### General information

#### Study withdrawal

No specific study withdrawal criteria have been set. Participants may withdraw from the study at any time for any reason. Should a HCP or stroke survivor decide to withdraw from the study, a reason for withdrawal will be sought but participants can chose to withdraw without providing an explanation. If a stroke survivor decides to withdraw, it will not affect the normal care they receive either now or in the future. Data collected prior to withdrawal will be used in the study analysis unless consent for this is specifically withdrawn.

Clinical teams, local treatment providers or investigators may also withdraw stroke survivors from the study at any time if they feel it is no longer in the participant’s interest to continue, for example, because of intercurrent illness.

#### Lone worker policy

Study team and intervention providers will follow the relevant Trust and/or Newcastle University lone workers policy when collecting study data and providing therapy in people’s homes.

#### Confidentiality

Personal data will be regarded as strictly confidential. The study will comply with the Data Protection Act, 2018, General Data Protection Regulations and Caldicott Principles. All study records will be kept at study sites and/or Newcastle University with restricted access. All trial documentation will be retained for future audit in line with the sponsor policies. Participants will not be identified in any report or publication arising from this research. Any feedback comments or quotes will be anonymised.

#### Indemnity

NHS Trusts participating in the study have liability for clinical negligence that harms individuals toward whom they have a duty of care. NHS indemnity covers NHS staff and academic staff with honorary contracts conducting the trial for potential liability in respect of negligent harm arising from the conduct of the study. Northumbria Healthcare NHS Foundation Trust is Sponsor, and through the Sponsor, NHS indemnity is provided in respect of potential liability and negligent harm arising from study management. Indemnity in respect of potential liability arising from negligent harm related to study design is provided by NHS schemes for those protocol authors who have their substantive contracts of employment with the NHS and by Newcastle University Insurance schemes for those protocol authors who have their substantive contract of employment with the university. This is a non-commercial study, and there are no arrangements for non-negligent compensation.

#### Data management

A web-based data entry tool will be developed and administered by the research team for the study. A database manager will monitor data quality under supervision of the project team.

### Data sharing

We will share anonymised data (referenced only with study number) with approved collaborators both nationally and internationally (inside and outside of the EU) for scientifically sound, peer-reviewed studies. Data sharing offers a more open approach which allows us to maximise the impact of the study for the health and well-being of the population.

Data sharing will be managed by our data management committee according to the following procedures:
Collaborators interested in accessing data from the study will send the data management committee an expression of interest, for example, using data request from or via research platforms data portals.The committee will then review the data request. If required, the data management committee may request changes to the proposed study by collaborators. The data management committee may then approve or reject the proposed study.A data use agreement will be drafted and signed by both parties.As agreed by the data managing committee and collaborators, and according to signed data agreement forms, anonymised data will be transferred to the collaborators.

Data will be securely transferred to collaborators. Data will be securely stored by collaborators for a fixed duration, as stated in the signed data use agreement. Only anonymous and unidentifiable data will be sent.

### Auditing

Progress and quality of trial delivery via fidelity checks will be monitored prospectively by the project management group at scheduled meetings. As this is a feasibility study, it will not be audited by an independent auditing company.

### Dissemination of results

The data will be the property of the Chief Investigator and Co-Investigator(s). Publication will be the responsibility of the Chief Investigator.

The study will be presented at national and international conferences and reported in peer-reviewed journals. Reports will be written for the study sponsor and regulatory bodies. A summary of the results will be sent to study participants. Anonymised data will be provided to research databases as requested (e.g. the Cochrane Collaboration, the Virtual International Stroke Trials Archive (VISTA) to enable future meta-analyses).

## Data Availability

See data sharing section above.

## Abbreviation

BCT: Behaviour change technique
HCPs: Healthcare professionals
SAE: Serious adverse event
TIDieR: Template for intervention description and replication
